### Hypotheses

#### Primary: effects of tDCS on inhibitory control and substance craving

Anodal tDCS over the right DLPFC as an add-on-therapy improves inhibitory control in SUD in comparison to anodal stimulation over the left DLPFC or occipital cortex, inhibition training, sham stimulation or TAU alone at T5 and T8.Anodal tDCS over the right DLPFC as an add-on-therapy increases fronto-central N200 and central-parietal P300 ERP amplitudes for substances cues and inhibitory control during task-associated EEG measurements at T5 and T8.Anodal tDCS over the right as well as the left DLPFC as an add-on-therapy reduces craving in SUD in comparison to stimulation over the occipital cortex, inhibition training, sham stimulation or TAU alone from T1 to T9.

#### Secondary: effects of tDCS as an add-on treatment in SUD

4.Anodal tDCS over the right DLPFC as an add-on treatment positively influences the treatment outcome (defined as abstinence or harm reduction) for SUD patients in comparison to stimulation over the occipital cortex, inhibition training, sham stimulation or TAU alone. Therefore, during the follow-up period (T6-T9), time to first relapse (treatment outcome: duration of abstinence) and amount of substance consumed (treatment outcome: harm reduction) is expected to be longer and less, respectively.

## Methods

### Sample size

The sample size estimation in based on the above-listed primary directed hypotheses. According to previous results on craving and inhibitory control [53, 54, 58, 60, 62], the effect size is estimated to be small to medium, f = 0.15. A sample size calculation was performed using the software G*Power http://www.gpower.hhu.de), which yielded 25 participants per group (power 80%, alpha 5%. repeated measures ANOVA and within-between interaction). In order to achieve this sample size, a total of 162 individuals (27 per group) will be assessed, whereby data losses are assumed (e.g., due to a lack of compliance, hardware failure).

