**Methods:**

This paper is a study protocol for a planned study. The study will enroll 162 treatment-seeking individuals aged 18 to 65 years who meet the DSM-5 criteria for alcohol use disorder (AUD), including those with other comorbid SUDs. Besides receiving treatment as usual (TAU), study participants will be randomly assigned to one of six groups: anodal stimulation over right dorsolateral prefrontal cortex (DLPFC; Group 1), left DLPFC (Group 2), or lateral occipital cortex (Group 3); sham tDCS (Group 4); computerized inhibition training (Group 5); or TAU only (Group 6). Assessments will be conducted at baseline (T1), across the directly following investigation days (T2-T4), post-intervention (T5), and at four follow-ups (after 4, 8, 12 and 24 weeks) at the Central Institute of Mental Health (Mannheim, Germany) and at the Psychiatric Center Nordbaden (Wiesloch, Germany). The primary outcomes include changes in craving and inhibitory control measured through a neuropsychological task (modified Go/No-Go task), as well as changes in electroencephalogram (EEG) activity during this task, specifically in event-related potentials including the N200 and P300 components. Secondary outcomes include abstinence days and amount of alcohol consumed.

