### Statistical analyses

The behavioral and EEG results of the inhibitory control paradigm [78] and craving ratings are defined as primary outcome measures. The results of the inhibitory control paradigm will be compared between testing days before (T1) and after fifth (T5) stimulation or training and after a follow-up period of 12 weeks (T8). Craving rates will be compared before and after the first stimulation/training (T1) and across the subsequent stimulation/training sessions (T2-T5), as well as during the follow-up period (T6-T9). Secondary outcomes include duration of abstinence and amount of substance consumed during the follow-up period.

Regarding the EEG data, resampling (to 250 Hz), filtering (70 Hz high- and 0.1 Hz low-pass filter; 50 Hz notch filter), re-referencing to an average reference, manual inspection, independent component analyses, and segmentation (from –200 to 1200 ms) will be conducted. Removed channels due to technical and regular artifacts (e.g., movement artifacts, excessive noise) will be interpolated using neighboring electrodes. ERP components will be scored as mean amplitudes between 200–300 ms and 300–500 ms over fronto-central and central-parietal electrodes for the N200 and P300 components, respectively. All data (EEG, neuropsychological and psychometric data) will be analyzed using t-tests, repeated measures analysis of variance (rmANOVA) and Pearson correlations. The influence of treatment modality (tDCS add-on intervention over various locations versus inhibition training versus standard treatment) on relapse will be tested with a Cox Regression (outcome variable: time until first relapse). Due to the included individuals and the matched-group design, potential influencing factors on primary and secondary endpoints (e.g., type of substance, severity of SUD, number of comorbidities) will be included in the analyses as covariates. In secondary analyses, we will also take a closer look at the potential influence of these factors on treatment response. In this way, it might be possible to identify subgroups that respond particularly well to the treatment (‘treatment responders’) with the goal of precision-targeted treatments for addiction. Statistical analysis will be conducted using SPSS (IBM Corp., Armonk, N.Y., USA).

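### The stated 80% power belongs to one undirected six-arm interaction test, not to the directed arm-versus-arm primary hypotheses it is said to support

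*Protocol article*

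**What the plan says.** The Sample size section of the protocol article opens: "The sample size estimation in based on the above-listed primary directed hypotheses". It then states that "the effect size is estimated to be small to medium, f = 0.15", and gives the G*Power result "which yielded 25 participants per group (power 80%, alpha 5%. repeated measures ANOVA and within-between interaction". To allow for losses, "a total of 162 individuals (27 per group) will be assessed, whereby data losses are assumed". Neither the number of measurements nor the correlation between them is given.

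The hypotheses are of a different kind. Hypothesis 1 states that right-DLPFC stimulation improves inhibitory control "in comparison to anodal stimulation over the left DLPFC or occipital cortex, inhibition training, sham stimulation or TAU alone at T5 and T8". Hypothesis 2 concerns N200 and P300 amplitudes at the same two visits. Hypothesis 3 sets right and left DLPFC against four other arms for craving, from T1 to T9. Under Statistical analyses, "The behavioral and EEG results of the inhibitory control paradigm [78] and craving ratings are defined as primary outcome measures". The task data are to be compared over T1, T5 and T8.

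**The concern.** A significant six-arm interaction shows only that change over time is not the same in all arms. It could arise because inhibition training does better than TAU, which says nothing about right DLPFC. So the test that was powered cannot establish any of the three primary hypotheses, although the section says it was sized for them. The calculation also spends 5% once, on one outcome, while task behaviour, ERPs and craving are all primary.

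The trial's conclusions will rest on particular contrasts, such as right against left or right against sham. With 80% on the page, a null result for one of these would be read as adequately powered evidence against an effect. A nominal success on one of several primary outcomes could also be reported as if it carried a 5% error rate.

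**Working it through.** **Inputs from the protocol article.** k = 6 arms, f = 0.15, alpha = 0.05, target power 0.80, 25 per group (N = 150), 27 per group enrolled (N = 162). **Not stated, so assumed:** number of measurements m, correlation r, sphericity (taken as met).

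**1. Reproducing 25 per group.** For the G*Power within-between interaction, the noncentrality is λ = N·m·f²/(1−r), with df1 = (k−1)(m−1) and df2 = (N−k)(m−1).

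- m = 2, r = 0.5, N = 150: λ = 150 × 2 × 0.0225/0.5 = 13.5, df 5 and 144, power 0.806. At N = 144 it is 0.786. So 25 per group.
- m = 3, r = 0.40, N = 150: λ = 150 × 3 × 0.0225/0.6 = 16.875, df 10 and 288, power 0.803. At N = 144 it is 0.782. Also 25 per group.
- m = 3, r = 0.5: N = 125, which is 21 per group.

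The stated figure is therefore an omnibus calculation, but it does not reveal which m and r were entered.

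**2. What f = 0.15 means for a pair of arms.** Take m = 2 and r = 0.5, so the SD of change equals the SD at one visit. The between-arm SD of mean change, in SD units, is then 2f = 0.30 (check: 150 × 0.30² = 13.5). The difference d between two arms depends on the pattern of means:

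- only right DLPFC differs: 0.30/√(1/6 × 5/6) = 0.805 SD
- right and left DLPFC differ equally from the other four (the craving pattern): 0.30/√(2/6 × 4/6) = 0.636 SD
- f = 0.15 read as a two-arm effect: 2 × 0.30 = 0.60 SD

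**3. Power of one pair at 25 per arm** (noncentral t on change scores, 48 df, noncentrality d√(25/2)):

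| Pattern | d | Two-sided 5% | One-sided 5% |
|---|---|---|---|
| Only right DLPFC differs | 0.805 | 0.80 | 0.88 |
| Right and left differ equally | 0.636 | 0.60 | 0.72 |
| f as a two-arm effect | 0.60 | 0.55 | 0.67 |

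Pooling the error over all six arms (144 df) adds about 0.01. With all 27 per arm analysed, the two-sided values are 0.83, 0.63 and 0.58. A two-sided pair at 25 per arm reaches 80% at d of about 0.81.

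In the most favourable pattern (d = 0.805), one two-sided pair at 0.05/5 has power 0.57 (0.59 pooled). Beating all five comparators at unadjusted 5% has power 0.51 to 0.53 by simulation.

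**4. Alpha over the primary set.**

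- Five unadjusted two-sided comparisons sharing the right-DLPFC arm, on one outcome at one visit, no true differences: probability of at least one false positive about 0.18 (simulation).
- Three or four independent primary outcomes, each tested once at 5%: 1 − 0.95³ = 0.143 and 1 − 0.95⁴ = 0.185.
- Dividing alpha instead, the omnibus test at 0.05/3 has power 0.66 at N = 150 and 0.71 at N = 162. It would need 189 analysed for 80%.

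**The case against.** The strongest replies are these.

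*The power loss is not universal.* This stands. If only right DLPFC differs, the pattern closest to hypothesis 1, a single unadjusted pair keeps about 0.80 two-sided and 0.88 one-sided. It is therefore wrong to say that every contrast falls short. The price is a 0.8 SD advantage over every other arm, which is hard to square with an effect described as small to medium, and hypothesis 3 implies a different pattern.

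*Multiplicity rules belong in an analysis plan that is not shown.* This also stands. The absence of a testing order or alpha split in a condensed article is no finding. It does not rescue the stated figure, because adjusting lowers the power and not adjusting raises the error.

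*Hypothesis 1 may not require beating all five comparators.* The text joins them with 'or' and states no success rule, so the 0.51 to 0.53 is an illustration of one reading.

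Two stronger readings are tempting and not supported. A reader might infer that the calculation used two visits although three are analysed. The figure does not show this, since three measurements with r of about 0.40 also return 25 per group. A reader might also count every comparator, visit and craving scale and infer that a false primary finding is very likely. That count needs comparators for hypothesis 2 that the text does not name, treats both craving scales as primary, picks visits for a hypothesis running from T1 to T9, and assumes that no pair is gated by the interaction test. The documents settle none of these.

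**Conclusion.** The point holds as a misattribution: an undirected omnibus calculation, tested once at 5% on one outcome, is presented as powering several directed primary hypotheses. The 25 per group is arithmetically sound for the omnibus test.

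For one arm-versus-arm claim at 25 per group, two-sided power runs from 0.55 to 0.80 according to the pattern of means, and from 0.67 to 0.88 if the directed wording is taken to mean one-sided 5% tests. Across several primary outcomes, 80% and 5% cannot both be claimed. The contrast figures assume two measurements, r = 0.5 and the protocol's own f = 0.15. Other values of the unstated inputs would change them, but would not turn an omnibus test into a directed one.

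**What to change.** In the Sample size section:

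- State that 80% refers to one omnibus arm-by-time interaction test on one outcome at 5%, and give the number of measurements and the correlation actually entered in G*Power.
- Add the power or detectable difference for a single two-arm contrast. Under the assumptions above, 25 per arm gives 80% two-sided power for about 0.81 SD in change.
- Stop describing the figure as based on the directed hypotheses.

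Where the analysis plan does not already do so, name one confirmatory contrast, outcome measure and visit for each primary hypothesis. Test these in a fixed order or with Holm at an overall 5%, and label the remaining comparators, visits and scales secondary. This should be settled before any outcome data are examined.

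The cost is wording, a less favourable stated power, and some comparisons moved to secondary status. No participants are added and no procedure changes.

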### Experimental procedure

*N* = 162 SUD patients, who voluntarily enter a qualified detoxification treatment program, will be examined (inpatient or day-clinic setting) at the Department of Addictive Behaviour and Addiction Medicine at the Central Institute of Mental Health in Mannheim, Germany and the Clinic for Addiction Therapy and Withdrawal at the Psychiatrisches Zentrum Nordbaden in Wiesloch, Germany. A randomized assignment (block randomization with permuted blocks of size 12) to one of six groups will be performed. All participants will be included during their second week of hospital stay to ensure completed detoxification (at least 7 days of abstinence) and enrollment in the treatment as usual (TAU). TAU comprises an at least three weeks long therapy duration including medical and therapeutic treatment. We will follow a placebo-controlled single-blind study design, in which participants do not receive any information about electrode placement or active vs. sham condition, except in the non-tDCS groups, namely group 5 (inhibition training) and group 6 (TAU).

Four groups will receive 20-min tDCS sessions using the Sooma Duo™ device (Sooma Oy, Helsinki, Finland) over five consecutive days at an intensity of 2 mA (≈0.08 mA/cm^2^). Electrodes (25 cm^2^) will be placed using a standardized EEG cap following the 10–20 system to ensure consistent positioning across sessions [44]. The current will be ramped up from 0.3 mA to 2 mA at 0.1 mA/s, maintained for 20 min during active stimulation. Stimulation sites will differ by group:

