## Discussion

Recent meta-analytic evidence shows that tDCS holds promise as a low-risk intervention for reducing substance craving, with right anodal DLPFC placement exerting more pronounced effects on craving reduction [73]. However, the current body of evidence is limited by the lack of direct comparisons between different anodal electrode placements as well as scarce research examining cognitive outcomes and underlying neurobiological mechanisms, which the present study aims to address. Given the central role of craving in relapse [102], integrating tDCS into existing SUD intervention and prevention strategies could provide a valuable tool for relapse prevention.

To ensure the success of the study, it will be critical to address common practical challenges. Participant discomfort, such as fatigue resulting from five consecutive investigation days, as well as high dropout rates frequently encountered in SUD treatment studies [103], will be proactively mitigated through regular check-ins and individualized support throughout the intervention, as needed. Qualified physicians and psychotherapists will be available to respond to any issues that arise to help create a supportive environment.

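### The 7.4% loss allowance is not justified against the protocol's own dropout and relapse risks, and the repeated measures ANOVA named for the primary outcomes risks resting on selected completers

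*Protocol article*

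**What the plan says.** The Sample size section assumes an effect for which "the effect size is estimated to be small to medium, f = 0.15", and reports a G*Power run "which yielded 25 participants per group (power 80%, alpha 5%. repeated measures ANOVA and within-between interaction". It then states that "a total of 162 individuals (27 per group) will be assessed, whereby data losses are assumed", with the examples "e.g., due to a lack of compliance, hardware failure". Loss to follow-up is not among the examples, and no expected retention is given.

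The primary hypotheses reach well beyond the treatment week. Inhibitory control is tested at T5 and T8. The EEG hypothesis is that right-sided stimulation "increases fronto-central N200 and central-parietal P300 ERP amplitudes for substances cues and inhibitory control during task-associated EEG measurements at T5 and T8". The craving hypothesis runs from T1 to T9. Table 1 and its legend place T8 on site at 12 weeks and T9 by telephone at 24 weeks.

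Under Statistical analyses, all EEG, neuropsychological and psychometric data "will be analyzed using t-tests, repeated measures analysis of variance (rmANOVA) and Pearson correlations", in SPSS.

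Three other places bear on loss:
- Risks and strengths of the study names dropout and relapse as the chief threats to completion, lets participants who relapse continue, and plans stepwise reimbursement.
- The Discussion refers to "high dropout rates frequently encountered in SUD treatment studies" and plans check-ins and individual support.
- The exclusion criteria list a breath alcohol concentration above zero at any examination.

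**The concern.** The allowance is small, and its stated reasons are not the ones the protocol treats as its main risk. Nothing connects 7.4% to retention at 12 or 24 weeks.

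The named method makes this matter more. In its classical form, repeated measures ANOVA needs every time point. A participant with T1 and T5 but no T8 leaves the whole analysis, so late loss also thins the end-of-treatment result.

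Loss at T8 is also unlikely to be random. Read literally, the breath-alcohol criterion removes a participant who is drinking at T8 from the task and EEG assessment, although the risk section says that someone who relapses may complete the study. Drinking is closely tied to craving and inhibitory control, and the secondary hypothesis expects stimulation to affect relapse. If it does, completers would be selected differently by arm and the randomised comparison would lose its protection.

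**Working it through.** **Inputs from the Protocol article.** f = 0.15, alpha 0.05, power 0.80, within-between interaction, 25 per group (Sample size). Six groups (k = 6): "A randomized assignment (block randomization with permuted blocks of size 12) to one of six groups will be performed" (Experimental procedure). Enrolment 162.

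**Inputs not in the document, therefore assumed.** Number of measurements m, correlation rho between them, sphericity (epsilon = 1), and the loss rate.

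**Allowance.** 6 × 25 = 150 analysable; (162 − 150)/162 = 12/162 = 7.4%.

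**Formula.** Noncentral F with lambda = f² × N × m/(1 − rho), df1 = (k − 1)(m − 1), df2 = (N − k)(m − 1).

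**Reproducing 25 per group.**
- m = 2, rho = 0.5, N = 150: lambda = 0.0225 × 150 × 2/0.5 = 13.5, df 5 and 144, power 0.806. The smallest N for 80% is 149.
- m = 3, rho = 0.4, N = 150: lambda = 0.0225 × 150 × 3/0.6 = 16.875, df 10 and 288, power 0.803. The smallest N for 80% is 150.
- m = 3, rho = 0.5, N = 150: power 0.883. This needs only N = 125, or 21 per group, so it does not reproduce the reported 25.

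**Power with 162 enrolled and listwise deletion.** N = 162 × (1 − loss); the loss rates are assumptions.

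| Loss | N | m = 2, rho = 0.5 | m = 3, rho = 0.4 | m = 3, rho = 0.5 |
|---|---|---|---|---|
| 7.4% | 150 | 0.81 | 0.80 | 0.88 |
| 10% | 145.8 | 0.79 | 0.79 | 0.87 |
| 20% | 129.6 | 0.73 | 0.73 | 0.82 |
| 30% | 113.4 | 0.66 | 0.65 | 0.75 |
| 40% | 97.2 | 0.58 | 0.56 | 0.66 |

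**Break-even loss.** For the two reproducing sets: 1 − 149/162 = 8.0% and 1 − 150/162 = 7.4%. For m = 3, rho = 0.5: 1 − 21/27 = 22.2% counted in whole groups, or 1 − 125/162 = 22.8%.

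**Enrolment that would keep 25 completers per group.** 25/(1 − loss), rounded up: 32 per group (192) at 20%, 36 (216) at 30%, 42 (252) at 40%.

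**Craving, as a check on over-reading.** If 10% were missing independently at each of T5 to T9, 0.9⁵ = 0.59 would be complete, about 96 of 162. With six measurements (T1, T5 to T9), rho = 0.5 and sphericity, the interaction test at N = 96 still has power of about 0.84; with epsilon 0.75 it is about 0.75. For craving, then, many incomplete records need not mean power below 80%. There the main issue is who is left in the analysis.

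**The case against.** A reader might infer that the stated 80% power is simply not met. The document does not support that. It gives no dropout rate, and the relapse range of 20–80% in the Background is not a loss rate, since participants who relapse may stay in the study. The Discussion's remark is about the field in general, and it comes with planned retention measures; T6, T7 and T9 need only a telephone call. The shortfall also depends on m and rho. The task has three occasions, and with m = 3 and rho = 0.5 power is still 0.82 at 20% loss. All of this stands, and it makes the size conditional. It does not explain 7.4%: no retention target is stated, and the favourable inputs would have called for 21 per group, not 25.

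It is also tempting to say that the plan prescribes a complete-case analysis. It does not use those words. Listwise deletion is inferred from how classical repeated measures ANOVA works, and rules for missing data may be in an analysis plan not shown here; their absence is no fault. Because t-tests are also listed, a T1-to-T5 comparison need not lose someone who misses T8. What remains is that the method the article names handles incomplete follow-up poorly. An analysis plan could change the method, but not the loss allowance already set in enrolment.

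Finally, the direction and size of any bias between arms cannot be derived from the document. Selective completion is a plausible risk, not a demonstrated bias.

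**Conclusion.** The point holds in conditional form. The allowance is 7.4%, and it is not justified against the protocol's own account of dropout and relapse, given primary outcomes at 12 weeks on site and, for craving, up to 24 weeks by telephone. On the two input sets that reproduce 25 per group, listwise power falls below 80% once loss passes about 7–8%. On more favourable inputs, which the reported sample size does not match, the margin is about 22%. These figures assume sphericity, f = 0.15, equal loss across groups and listwise deletion.

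The risk of selected completers at T8 does not depend on those power inputs. It follows from the named method together with an exclusion that is triggered by drinking. Its size is unknown.

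**What to change.** - **Analysis.** For the primary outcomes, replace repeated measures ANOVA with a likelihood-based linear mixed model, available in SPSS, on all randomised participants as allocated. Use post-baseline values as outcome; include group, visit, group × visit and the T1 value as covariate; and specify contrasts at T5 and T8 for the task and EEG. Extend the visits to T9 for craving.
- **Power.** State that 80% applies only at the retention that delivers 25 analysable per group. Report m, rho and the expected T8 and T9 retention, with power computed for the analysis actually planned. The percentages under the working are for an omnibus listwise ANOVA and must not be carried over as power for a T8 contrast in the mixed model.
- **Consistency.** Reconcile the breath-alcohol exclusion at any examination with the statement that participants may complete the study after relapse, so that it is clear whose T8 data are collected and analysed.

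**Cost.** Mainly wording, plus a rerun of the power calculation. The model relies on data being missing at random given what it contains. Relapse between T5 and T8 is not in it, so that assumption could fail, and a participant with no value after T1 adds no outcome data. The restated power may look less favourable; if so, the choice between more enrolment and lower stated power becomes explicit.
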